#### Tertiary objective – effects of treatment on quality of life

The aim of addiction treatment is recovery which can be defined as abstinence plus improved quality of life [40]. Therefore, quality of life will be assessed in addition to the drinking related variables mentioned above (see Table 1).

#### Quarteniary objectives – safety, acceptability and feasibility of treatment

Expectancies and experiences about treatment of both participants and therapists may affect treatment outcome. Therefore harm expectancy and experience, expected and experienced burden, credibility of treatment and treatment adherence will be assessed.

## Methods/design

### Design

This study is a randomized controlled trial with two arms: EMDR + TAU versus TAU. The two groups are compared pre-treatment (T0), post treatment (T1 = T0 + 8 weeks) and at follow up one (T2) and six months (T3) post treatment, on variables linked to the research questions. This amounts to a 2 × 4 design with the between factor condition (EMDR + TAU vs. TAU) and within factor time (pre- x post intervention × 1 × 6 months follow-up).

Both groups will be assessed at the same time-points, whereby a substantial part of both groups may still receive TAU at follow-up after 1 month, but may no longer receive TAU at follow-up after 6 months.

The current study is hybrid in that it tries to broaden the generalizability of the outcomes by recruiting a representative, but complex sample while maintaining some of the rigor of efficacy research (e.g. using training and supervision, monitoring of and feedback on treatment fidelity). This allows to analyze data from an effectiveness (outcome in real life circumstances, using all data, including imputed data in case of study drop-out etc.) and an efficacy (outcome under ideal circumstances using only completers data) viewpoint.

The design of this study was approved by the Medical Ethics Committee of Medisch Spectrum Twente and is registered as study NL43892.044.13.

### Participants and recruitment

Adult patients, 18 years or older, with a primary DSM-IV-TR [41] diagnosis of alcohol dependence or abuse are recruited from six outpatient sites of IrisZorg, an addiction treatment organization in the Netherlands. The trial process starts with a global identification of possible eligible patients (on the basis of known in- and exclusion criteria, see next paragraph) by a triagist when they seek treatment. If they agree to be informed about the study, they are contacted by a research assistant (RA1, a psychologist) to provide additional information and to answer questions. Participants consent to postponed information after they receive limited oral and written information to be able to blind them as much as possible from later group allocation using the procedure outlined by [42]. After consent, an appointment is made for an inclusion interview. If included, participants undergo a pre-treatment assessment (T0) (see Figure 1).

**Figure 1 Fig1:**
[figure not shown]
**Flow Diagram RCT.**

### Inclusion and exclusion

The inclusion criteria are:Age 18 or older;Fluent in Dutch speaking and reading abilities (clinical observation by RA1) and;A primary DSM-IV-TR diagnosis of alcohol dependence or abuse.

This last criterion is assessed during the regular intake procedure by a health care or clinical psychologist.

Exclusion criteria are:Meeting the DSM-IV-TR criteria for current PTSD;Meeting the DSM-IV-TR criteria for current dependence and regular (at least once per week in the last 2 weeks before eligibility screening) use of substances other than alcohol or nicotine;Current (in the last two weeks before eligibility screening) regular alcohol use (at least > 21E (women) or > 28E (men) per week) and;Severe, current (since the start of regular treatment) psychiatric symptoms (especially manic, psychotic, suicidal and aggressive symptoms) that interfere with TAU.

These criteria are assessed during intake by a health care or clinical psychologist and/or (re)assessed by RA1 during screening. RA1 uses segments of the Mini-International Neuropsychiatric Interview-Plus (MINI-Plus [43]), the Measurements in the Addictions for Triage and Evaluation (MATE 2.1 [44]) and/or clinical observation as well as information from the patients dossier.

When RA1 detects psychopathology not detected during regular intake, the participant is informed as well as his/her regular therapist to ensure further diagnostics and treatment is provided, if necessary.

### Randomization and allocation

After inclusion, participants are randomized to either EMDR + TAU or “TAU only” by another RA (RA2, a psychologist), not involved in the assessments. Participants are allocated to their treatment condition based on a randomization code. RA2 generates a randomization sequence before the recruitment phase starts using freely available software [45].

The randomization sequence is stratified by participating facility (a total of six sites), further subdivided by a maximum of three care pathway (‘youth’ (youngsters up to 23 years old), ‘addiction’ (adult patients with primarily addiction) or ‘addition, care and housing’ (adult patients with problems on multiple life domains in addition to addiction and often severe psychiatric problems), if there is a participating EMDR therapist available in that striatum. EMDR therapists may work at multiple facilities and/or care pathways and thus see participants from different strata. This amounts to a stratified randomization with a 1:1 group allocation within each stratum, using block sizes of 4.

When participants are allocated to TAU only, no action is taken (since RA1 already planned subsequent assessments, independent of allocation). When they are allocated to EMDR + TAU, RA2 informs participants by email about EMDR with additional written information. RA2 also informs a participating EMDR therapist of the same facility where the participant receives TAU. The EMDR therapist contacts the participant and provides additional information about EMDR to the participant and plans seven weekly EMDR sessions.

Great care is taken so that all those involved in the study are blinded as much as possible. Participants, RA1 (the assessor) and the principal investigator are blinded to group allocation while EMDR therapists are blinded to outcome of assessments. In addition, the principal investigator was not involved in the treatment of participants.

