### Power and sample size calculation

Since two active treatment arms are compared and the sample is expected to be relatively heterogeneous regarding baseline variables such as dependence severity, drinking status and other substance use, it is estimated that the effect size will be relatively small. Clinical relevant differences on the primary outcome variable (changes in number of heavy drinking days in the previous 30 days) were calculated on the basis of data of a recent study [46]. In patients with an alcohol-use disorder referred to in- or outpatient alcohol treatment the mean baseline score for heavy drinking days (≥5 drinks in a single day, over the past 30 days) was 16.33 (SD 11.99). Treatment outcome was such that undertreated patients (<75% attendance of the number of sessions recommended by treatment allocation guidelines, n = 618) showed a reduction of 8.7 heavy drinking days (±12.5) while overtreated patients (>110% attendance of sessions recommended) showed a reduction of 12.5 heavy drinking days (±12.2, n = 362). The difference between under- and overtreated patients is at least 3.8 heavy drinking days over the past 30 days which corresponds to an effect size of *d* = 0.31 or *f* = 0.15).

Subsequent poweranalysis in G*Power version 3.1.2. [47] (ANOVA: repeated measures, within-between interaction) indicated a sample size of 74 to demonstrate this effect (keeping α at 0.05 and power at 0.80 and using 2 groups and 3 measurements (concerning changes in the number of heavy drinking days between 4 time points)). Attrition is estimated to be relatively high at 33%. Therefore we add 26 participants (100 patients in total, 50 in each treatment arm), to meet the required sample size.

To minimize missing values RA1 will use email, text messages, telephone calls, and/or contacts with participants’ regular therapists to remind participants about their assessment appointments. All participants will receive financial compensation of 25 euros (in the form of a gift cheque) for every complete assessment at T2 and T3, regardless of whether or not the participant drops out of treatment.

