### Eye movement desensitization and reprocessing (EMDR)

Participants allocated to the EMDR + TAU group will receive a manualized intervention. This set of EMDR protocols was developed by the principal investigator and the EMDR International Association (EMDRIA)-approved consultant involved in this study as a trainer. It incorporates elements of existing EMDR addiction protocols [35,37,38], related work [51] and insights on positive and prospective memory representations [19,20]. Based on pilot treatments, the intervention manual was fine-tuned before the recruitment phase.

Participants receive a maximum of seven weekly, 90-minute EMDR sessions provided by health care psychologists (who at least completed an EMDRIA-approved Basic Training program). The EMDR therapists will be trained in the use of the intervention manual and will be supervised monthly by the EMDR consultant. All EMDR sessions are video-recorded for fidelity rating and supervision.

Session one starts with instruction on some rules and the rationale for EMDR and its use in addiction. Then the treatment goal (controlled drinking or abstinence) is established. Subsequently participants are instructed to imagine their positive treatment goals vividly. After that both negative associations with long-term abstinence (if present) and positive memories associated with alcohol use are targeted with EMDR. At the end a homework diary is presented and participants are instructed to keep it daily, between sessions. It helps to register daily craving, alcohol use, possible adverse and/or positive events and help participants to prepare for the next session by identifying possible targets. Subsequent sessions focus on memory representations associated with loss of control, self-efficacy undermining beliefs, trigger situations, and anticipated relapse. Finally the focus shifts to feeling more empowered in trigger situations. Therapists are instructed to keep the duration of sessions as constant as possible, selecting only the most relevant targets. In some cases, fewer sessions may be required and provided.

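### Fixed, disclosed blocks of 4 in small strata make about 22–33% of assignments certain to anyone who knows the stratum's earlier assignments; concealed, varying block sizes would remove most of that certainty

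*Protocol article*

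**What the plan says.** All references are to the protocol article.

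- **Block rule** (Randomization and allocation): "This amounts to a stratified randomization with a 1:1 group allocation within each stratum, using block sizes of 4".
- **Strata** (same section): "The randomization sequence is stratified by participating facility (a total of six sites), further subdivided by a maximum of three care pathway", with the restriction "if there is a participating EMDR therapist available in that striatum". Eighteen is therefore a maximum.
- **Total** (Power and sample size calculation): "Therefore we add 26 participants (100 patients in total, 50 in each treatment arm), to meet the required sample size".
- **Who allocates** (Randomization and allocation): randomisation follows inclusion and is done "by another RA (RA2, a psychologist), not involved in the assessments". RA2 also generates the sequence, before recruitment starts. Participants, RA1 and the principal investigator are listed as blinded; intake psychologists and regular therapists are not on that list.
- **Who learns of an EMDR allocation** (same section): the participant is emailed information about EMDR, and "RA2 also informs a participating EMDR therapist of the same facility where the participant receives TAU". For a TAU-only allocation nothing is done.
- **Who judges eligibility** (Inclusion and exclusion): "These criteria are assessed during intake by a health care or clinical psychologist and/or (re)assessed by RA1 during screening". Clinical observation is among the permitted means.
- **Who treats** (Eye movement desensitization and reprocessing): "90-minute EMDR sessions provided by health care psychologists".
- **Contact after allocation** (Data collection; Measurements – safety, acceptability and feasibility): RA1 repeats the measurements at T1, T2 and T3, and participants are asked at each time-point about the treatment they are having and about adverse events.
- **Trial status**: recruiting.

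**The concern.** Central allocation by RA2 hides the list, but it does not stop a reader from deducing the next entry. With 1:1 blocks whose size is always 4 and publicly known, a block's last place always follows from the first three, and its third place follows whenever the first two match. Small strata accrue slowly, so earlier places in a block may be known before the next patient is screened.

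If a person with a say in eligibility could make that deduction, a patient with a better outlook could be steered toward EMDR + TAU, or a difficult one put off or excluded. Some criteria leave room for judgement, such as fluency in Dutch and psychiatric symptoms that get in the way of TAU. Intention-to-treat analysis and the planned stratum covariate do not undo selection at entry. The primary outcome is self-reported and the planning effect is small (d = 0.31), so modest steering could matter.

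**Working it through.** The article gives no predictability figure to reproduce. The inputs are its block size (4), ratio (1:1), maximum number of strata (6 × 3 = 18) and total (100).

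**1. One complete block of 4.** There are six equally likely orders: EETT, ETET, ETTE, TEET, TETE, TTEE. An assignment is certain when one arm has already used its two places.
- Position 1: probability certain 0. Position 2: 0. Position 3: 2/6 = 1/3 (EETT, TTEE). Position 4: 1.
- Share certain = (0 + 0 + 1/3 + 1)/4 = 33.3%.
- Best-guess accuracy by position is 1/2, 2/3, 2/3, 1. The mean is 2.833/4 = 70.8%, against 50% with no information.

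**2. Incomplete last blocks.** A stratum that stops early in a block has a lower share.

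| Patients in stratum | Certain assignments | Share certain | Best guess |
|---|---|---|---|
| 4 | 1.333 | 33.3% | 70.8% |
| 5 | 1.333 | 26.7% | 66.7% |
| 6 | 1.333 | 22.2% | 66.7% |
| 8 | 2.667 | 33.3% | 70.8% |

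**3. The whole trial of 100.**
- 18 strata: mean 100/18 = 5.6 patients. An even spread is ten strata of 6 and eight of 5, giving 18 × 1.333 = 24 certain assignments. With uneven strata the figure is about 26–27.
- 12 strata: about 28–32.
- 6 strata: about 31–32.
- A single list: 33.

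So one third belongs to complete blocks or few strata, and about a quarter belongs to 18 strata.

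**4. How soon the history is known.** Steps 1–3 assume immediate and complete knowledge. The accrual period is not stated. Simulating an assumed 12 to 36 months with 6 to 18 even strata gave about 22–31% certain if every assignment is known after one week, and about 3–23% if known only at T1, eight weeks later.

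**5. The alternative.** Randomly mixed blocks of 4 and 6, equally likely, with the order of sizes concealed and history fully known (exact enumeration):

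| Patients in stratum | Certain: fixed 4 | Certain: mixed 4/6 | Best guess: fixed 4 | Best guess: mixed 4/6 |
|---|---|---|---|---|
| 4 | 33.3% | 1.3% | 70.8% | 65.4% |
| 5 | 26.7% | 5.0% | 66.7% | 64.3% |
| 6 | 22.2% | 7.5% | 66.7% | 67.2% |
| 8 | 33.3% | 5.9% | 70.8% | 66.8% |
| 17 | 31.4% | 5.9% | 69.6% | 67.8% |

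Certainty falls sharply. Guessability falls by a few percentage points at most, and in a stratum of 6 it does not fall at all.

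**The case against.** A reader might infer that the staff who judge eligibility know earlier assignments, and so that up to a third of assignments are open to manipulation. The article does not support that.

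- RA1, who screens and holds the inclusion interview, is stated to be blinded, and allocation comes only after inclusion.
- Intake happens when a patient enters regular care, and RA1 makes the inclusion appointment. Intake psychologists are not shown to control the order of entry within a stratum.
- That intake staff and EMDR therapists may share a profession does not show that they are the same people or exchange allocations.
- Certainty needs the full ordered history, including TAU-only patients, who trigger no notice. An EMDR therapist alone sees only part of the sequence.
- Severity and motivation are measured by T0 and compared between arms, and CDT and GGT back up self-report. These would help to reveal selection, though they would not remove it.

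All of this stands, and it limits the point to a conditional risk. What it does not do is close the route. RA1 plans the assessments and so can know who was included and when. From T1 RA1 also asks participants about their treatment, and EMDR participants know that they receive EMDR. For someone who knows the inclusion list, absence of EMDR means TAU. No statement says that intake staff or regular therapists are kept from earlier allocations.

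**Conclusion.** The point holds as a conditional weakness with a cheap remedy. A fixed, disclosed block of 4 makes about 22–33% of assignments certain, depending on stratum size, and about 24–27% if 18 strata are used. This assumes complete and prompt knowledge of the stratum's history; slower knowledge lowers the share, under assumed accrual, to as little as 3%.

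Two stronger readings should be avoided. The article contains no evidence of a leak to those who judge eligibility. And the one-third figure should not be paired with 18 strata, because the two do not occur together. The remedy should not be oversold either: it removes near-certainty, while informed guessing stays well above 50%.

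**What to change.** For every block not yet opened, RA2 regenerates the sequence with randomly varying block sizes, for example 4 and 6, known only to RA2. In the section on randomization and allocation, the phrase giving block sizes of 4 becomes: randomly varying block sizes not disclosed to those who screen or treat. Because best-guess accuracy barely moves, it would help to add a sentence saying whether intake staff and regular therapists are kept from earlier allocations.

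The cost is minutes of RA2's time and a sentence or two in an amendment, with no extra patients or staff. There are two drawbacks. Chance imbalance within very small strata rises slightly, which the planned stratum covariate already addresses. And if many strata are in use, each holds only one or two blocks, so a change during recruitment reaches few remaining patients.

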### Power and sample size calculation

Since two active treatment arms are compared and the sample is expected to be relatively heterogeneous regarding baseline variables such as dependence severity, drinking status and other substance use, it is estimated that the effect size will be relatively small. Clinical relevant differences on the primary outcome variable (changes in number of heavy drinking days in the previous 30 days) were calculated on the basis of data of a recent study [46]. In patients with an alcohol-use disorder referred to in- or outpatient alcohol treatment the mean baseline score for heavy drinking days (≥5 drinks in a single day, over the past 30 days) was 16.33 (SD 11.99). Treatment outcome was such that undertreated patients (<75% attendance of the number of sessions recommended by treatment allocation guidelines, n = 618) showed a reduction of 8.7 heavy drinking days (±12.5) while overtreated patients (>110% attendance of sessions recommended) showed a reduction of 12.5 heavy drinking days (±12.2, n = 362). The difference between under- and overtreated patients is at least 3.8 heavy drinking days over the past 30 days which corresponds to an effect size of *d* = 0.31 or *f* = 0.15).

Subsequent poweranalysis in G*Power version 3.1.2. [47] (ANOVA: repeated measures, within-between interaction) indicated a sample size of 74 to demonstrate this effect (keeping α at 0.05 and power at 0.80 and using 2 groups and 3 measurements (concerning changes in the number of heavy drinking days between 4 time points)). Attrition is estimated to be relatively high at 33%. Therefore we add 26 participants (100 patients in total, 50 in each treatment arm), to meet the required sample size.

To minimize missing values RA1 will use email, text messages, telephone calls, and/or contacts with participants’ regular therapists to remind participants about their assessment appointments. All participants will receive financial compensation of 25 euros (in the form of a gift cheque) for every complete assessment at T2 and T3, regardless of whether or not the participant drops out of treatment.

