### Interventions

#### Treatment as usual (TAU)

All participants already receive TAU at the moment they are enrolled and will continue to receive TAU for as long as indicated by their regular therapists but at least until T1. TAU may differ in intensity or additional components delivered (e.g. family treatment) between participants. In IrisZorg, most out-patients of care pathway ‘youth’ and ‘addiction’ receive (Adolescent) Community Reinforcement Approach ((A)CRA) treatment, consisting of several interventions, based on behavioral therapy principles [48]. Elements may include: functional analysis, training communication and/or problem-solving skills, sobriety sampling, social networking, learning to refuse substances, increasing alternative reinforcing activities, relapse management and medication monitoring. Treatment is individual but may also be partly groupwise. Patients receive TAU on a weekly basis by a health care worker.

Alternatively, some patients in care pathway ‘young’ may receive an intensive family treatment for youngsters up to 20 years old (and their families), who still live at home (or intend to go back to live at home again) and where multiple life domains may be affected (e.g. family, school, mental health, criminal behavior etc.): Multidimensional Family Therapy (MDFT [49]). Patients of care pathway ‘addition, care and housing’ receive Function Assertive Community Treatment (FACT [50]), a multidisciplinary, outreaching approach aimed at stabilization, treatment and recovery.

TAU is supervised by a clinical psychologist or psychiatrist. If necessary, treatment may be supplemented with medical care (such as, but not limited to medication), individual psychological care or relationship or family therapy. Incidentally or periodically, additional in-patient treatment may be necessary. CRA and MDFT typically lasts 6 months (in some cases CRA may be limited to 3 or extended to 9 months) while FACT may endure much longer.

‘Time-in-treatment’ before intervention and during the course of the study as well as main components and treatment intensity of TAU will be registered. The use of psychofarmaca, craving reducing (acamprosate, naltrexone) or abstinence enforcing medication (disulfuram) will be monitored.

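### The 3.8-day target and 80% power come from patients at referral averaging 16.33 heavy drinking days; the trial's drinking cap and in-treatment enrolment make that baseline unlikely, so neither is supported for the enrolled patients

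*Protocol article*

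**What the plan says.** All references are to the protocol article.

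- **Power and sample size calculation.** The source patients are described thus: "In patients with an alcohol-use disorder referred to in- or outpatient alcohol treatment the mean baseline score for heavy drinking days", with the count given as "over the past 30 days) was 16.33 (SD 11.99". The undertreated group (n = 618) "showed a reduction of 8.7 heavy drinking days (±12.5"; the overtreated group "showed a reduction of 12.5 heavy drinking days (±12.2, n = 362". The target follows: "The difference between under- and overtreated patients is at least 3.8 heavy drinking days over the past 30 days". Its standardised size is then stated in these words: "which corresponds to an effect size of *d* = 0.31 or *f* = 0.15". G*Power then gives 74 patients (alpha 0.05, power 0.80, 2 groups, 3 measurements), raised to 100 for 33% attrition.
- **Inclusion and exclusion.** One exclusion criterion is "Current (in the last two weeks before eligibility screening) regular alcohol use (at least > 21E (women) or > 28E (men) per week".
- **Treatment as usual (TAU).** "All participants already receive TAU at the moment they are enrolled".
- **Objectives.** A heavy drinking day means 5 or more standard drinks, and time to first drink applies only to participants who have reached abstinence.

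The article gives no expected T0 level of heavy drinking days for its own participants. It does not adjust the 3.8 days or the SDs for the cap or for treatment already under way.

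**The concern.** The source patients were measured at referral, with no drinking cap mentioned. The trial's patients are measured later and after selection: the heaviest current drinkers are removed, and some of the fall that the source recorded after baseline may already have happened before T0. Both features push the T0 mean down and leave fewer days by which the arms can differ.

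If the target is too large for these patients, the stated power is too high, and a null result could be read as evidence against EMDR when the trial was not powered for the difference it could plausibly show. This is separate from how the effect size was entered in G*Power: a corrected entry would still carry over 3.8 days and the source SDs.

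**Working it through.** **1. Reproducing the plan's figure.** Pooled SD of change = sqrt((617 × 12.5² + 361 × 12.2²)/978) = 12.39, so d = 3.8/12.39 = 0.307 and f = d/2 = 0.153, matching 0.31 and 0.15. For the within-between interaction, lambda = f² × N × m/(1 − rho), df1 = (k − 1)(m − 1) and df2 = (N − k)(m − 1), with k = 2 and m = 3. The article gives no rho; with rho = 0.5 and f = 0.15, N = 74 has power 0.806 and N = 72 has 0.795. So 74 reproduces. The steps below keep this test, rho = 0.5 and f = d/2.

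**2. What the cap allows.** Most heavy days per 30 for someone exactly at the cap throughout = (weekly cap × 30/7)/(drinks per heavy day):

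| Drinks per heavy day | Women (21) | Men (28) |
|---|---|---|
| 5 (the definition) | 18 | 24 |
| 8 (assumed) | 11.3 | 15.0 |
| 10 (assumed) | 9.0 | 12.0 |

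A mean of 16.33 needs at least 16.33 × 5 × 7/30 = 19.05 units per week, with every heavy day at exactly 5 drinks and no other drinking. That is 91% of the women's cap and 68% of the men's, as an average over all participants. Daily heavy drinking (at least 35 units per week) exceeds both caps, so the top of the source distribution is cut off.

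The cap covers only 14 days. With 16 days at the source rate (16 × 16.33/30 = 8.7) and 14 days at the cap with 8 drinks per heavy day (42/8 = 5.25 for women, 56/8 = 7 for men), the total is 14.0 or 15.7.

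**3. A plausible T0 mean after the cap.** As an illustration, take a beta-binomial on 0 to 30 days with mean 16.33 and SD 11.99 (a = 0.317, b = 0.266; the shape is an assumption). Keep only patients with at most 8 (women, 42/5) or 11 (men, 56/5) heavy days in 14. This is lenient: exactly 5 drinks per heavy day, no other drinking, no effect of earlier TAU. The remaining mean and SD are about 5.4 and 5.9 (women) and 8.2 and 8.3 (men). The mean falls to 33% and 50% of the source value, the SD only to 49% and 69%.

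**4. Effect on the difference and the power.** If the source reductions scale with baseline b, the difference is b × 3.8/16.33 = 0.233b. This treats both source subgroups as starting from 16.33, which the article does not state. Power at N = 67 / 74 / 100:

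| T0 mean | Difference (days) | SD of change stays 12.39 | SD shrinks with square root of mean | SD shrinks in proportion |
|---|---|---|---|---|
| 12.5 | 2.9 | 0.54 / 0.58 / 0.73 | 0.66 / 0.71 / 0.84 | 0.78 / 0.82 / 0.93 |
| 8 | 1.9 | 0.25 / 0.27 / 0.35 | 0.46 / 0.50 / 0.64 | 0.78 / 0.82 / 0.93 |
| 4 | 0.9 | 0.09 / 0.10 / 0.12 | 0.25 / 0.27 / 0.36 | 0.78 / 0.82 / 0.93 |

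In the step 3 illustration, if the SD of change shrinks as the T0 SD does, d = 0.233 × 5.4/(12.39 × 0.49) = about 0.20 for women and 0.233 × 8.2/(12.39 × 0.69) = about 0.22 for men. Power at N = 74 is then about 0.46 and 0.54.

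**The case against.** Three stronger readings are tempting, and the case against each is good.

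- **That the criteria rule out a mean of 16.33.** They do not. At the defining 5 drinks the cap permits 18 or 24 heavy days, it covers only two weeks of a 30-day window, and the time already spent in TAU is unspecified: patients are first identified when they seek treatment. Drinks per heavy day are not given. The supportable word is unlikely.
- **That 3.8 days cannot be reached.** If TAU removed a further 8.7/16.33 = 53% after T0, the largest possible gap would be 0.467b, which is below 3.8 for b under 8.1. But if part of that fall came before T0, less remains afterwards: the threshold 3.8/(1 − TAU fraction) becomes 5.1 at 25% and 3.8 at 0%. Relapse also counts. The Background cites relapse in more than 85% of patients within a year, and the Discussion makes reducing relapse part of the main goal. If drinking rises again under TAU, the arms can differ by 3.8 days from a low T0 mean.
- **That the stated power is definitely wrong.** Power was computed on the standardised f, and a restricted sample should have a smaller SD too. If the SD of change shrinks in full proportion to the mean, power stays near 0.80.

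All three limits stand. They do not supply the missing justification. The last needs proportional shrinkage, which the article neither states nor supports, and even then the difference detected would be smaller than the 3.8 days presented as clinically relevant.

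**Conclusion.** The concern holds in a limited form. The 3.8-day target, d = 0.31 and 80% power describe patients at referral, and the article's own cap and in-treatment enrolment make their T0 mean unlikely here. For the enrolled patients the target and power are unsupported. Power may be well below 0.80: at N = 74 it runs from 0.10 to 0.82 across T0 means of 4 to 12.5, and is about 0.46 to 0.54 in the truncated illustration. It stays near 0.80 only if the SD of change falls in proportion to the baseline mean.

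These sizes rest on assumptions about the T0 level, drinks per heavy day, equal subgroup baselines in the source, rho = 0.5 and, for the illustration, the beta-binomial shape. They show that the stated power is fragile; they do not predict the trial's actual power.

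**What to change.** In Power and sample size calculation:

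1. Replace the source baseline and SD with the pooled, arm-blinded T0 mean and SD of heavy drinking days from participants already enrolled. The Trial status section says that data collection has started.
2. Add the pooled, blinded SD of change, or the between-visit correlation, from visits already completed. If too few are complete, state an assumed range. T0 data alone cannot give power for a test of change.
3. Restate the target difference on that scale, for example as a proportional contrast, with its assumptions.
4. Report power for N = 100 and for the 67 left after 33% attrition (100 × 0.67). That is below the 74 required; on the plan's own f = 0.15 its power is about 0.76.

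No added enrolment and no change to eligibility or treatment is proposed. The cost is one blinded descriptive run and a reworded paragraph. The downside is a less favourable stated power or detectable effect.
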